# The efficacy of a multimodal physical activity intervention with supervised exercises, health coaching and an activity monitor on physical activity levels of patients with chronic, nonspecific low back pain (Physical Activity for Back Pain (PAyBACK) trial): study protocol for a randomised controlled trial

**DOI:** 10.1186/s13063-017-2436-z

**Published:** 2018-01-15

**Keywords:** Low back pain, Physical activity, Exercise therapy, Health coaching, Activity monitor

## Abstract

**Background:**

Physical activity plays an important role in the management of chronic low back pain (LBP). Engaging in an active lifestyle is associated with a better prognosis. Nevertheless, there is evidence to suggest that patients with chronic LBP are less likely to meet recommended physical activity levels. Furthermore, while exercise therapy has been endorsed by recent clinical practice guidelines, evidence from systematic reviews suggests that its effect on pain and disability are at best moderate and not sustained over time. A limitation of current exercises programmes for chronic LBP is that these programmes are not designed to change patients’ behaviour toward an active lifestyle. Therefore, we will investigate the short- and long-term efficacy of a multimodal intervention, consisting of supervised exercises, health coaching and use of an activity monitor (i.e. *Fitbit Flex*) compared to supervised exercises plus sham coaching and a sham activity monitor on physical activity levels, pain intensity and disability, in patients with chronic, nonspecific LBP.

**Methods:**

This study will be a two-group, single-blind, randomised controlled trial. One hundred and sixty adults with chronic, nonspecific LBP will be recruited. Participants allocated to both groups will receive a group exercise programme. In addition, the intervention group will receive health coaching sessions (i.e. assisting the participants to achieve their physical activity goals) and an activity monitor (i.e. *Fitbit Flex*). The participants allocated to the control group will receive sham health coaching (i.e. encouraged to talk about their LBP or other problems, but without any therapeutic advice from the physiotherapist) and a sham activity monitor. Outcome measures will be assessed at baseline and at 3, 6 and 12 months post randomisation. The primary outcomes will be physical activity, measured objectively with an accelerometer, as well as pain intensity and disability at 3 months post randomisation. Secondary outcomes will be physical activity, pain intensity and disability at 6 and 12 months post randomisation as well as other self-report measures of physical activity and sedentary behaviour, depression, quality of life, pain self-efficacy and weight-related outcomes at 3, 6, and 12 months post randomisation.

**Discussion:**

This study is significant as it will be the first study to investigate whether a multimodal intervention designed to increase physical activity levels reduces pain and disability, and increases physical activity levels compared to a control intervention in patients with chronic LBP.

**Trial registration:**

ClinicalTrials.gov, ID: NCT03200509. Registered on 28 June 2017.

**Electronic supplementary material:**

The online version of this article 10.1186/s13063-017-2436-z) contains supplementary material, which is available to authorized users.

## Background

Low back pain (LBP) is the leading cause of years lived with disability worldwide [1], with an estimated point prevalence of 18.3% [2]. Nonspecific LBP is the most common form of LBP and the term ‘nonspecific’ means that the pathoanatomical cause is unknown [3]. Although most patients with acute LBP find that their symptoms improve in the first 6 weeks [4], about 40% of them may develop chronic and persistent symptoms [5]. Nearly 60% of these patients continue to report moderate levels of pain and disability after 1 year [6]. Emerging evidence suggests the coexistence of chronic LBP and cardiovascular comorbidities such as obesity [7] and cardiovascular diseases [8]. Hence, health care professionals are now facing the challenge of using evidence-based interventions that also manage and prevent comorbidities in this population such as interventions that aim to increase physical activity levels [9].

Physical inactivity is commonly associated with chronic LBP. There is evidence to suggest that patients with chronic LBP are less likely to meet the recommended physical activity levels [10] and are considered less active compared to individuals without LBP [11]. In addition, active patients with LBP have a better prognosis compared to sedentary patients [12]. Although exercise therapy has been endorsed by recent clinical practice guidelines [13], its effect on pain and disability are at best moderate and smaller over time [14]. A systematic review from our group shows that most physical activity-based interventions failed to increase objectively measured physical activity levels of patients with chronic musculoskeletal pain [15]. We would argue that current interventions are not designed to change patients’ behaviour toward an active lifestyle.

Behaviour-change interventions involve a range of techniques and have been advocated to change physical activity behaviour [16]. Health coaching is a behaviour-change strategy defined as the practice of health education and health promotion within a coaching context, to enhance the well-being of individuals and to facilitate the achievement of their health-related goals [17]. This strategy has been considered effective to promote physical activity among the general population [18] and among patients with acute and subacute LBP [19]. Moreover, one technique commonly incorporated in interventions to promote physical activity is the provision of feedback. Recently, wearable physical activity monitors, such as the *Fitbit*, have been used to provide interactive feedback and individualised support on real-time physical activity behaviour (e.g. step counts). Interventions incorporating wearable devices to provide feedback on physical activity have been shown to be effective in promoting weight loss among obese participants [20] as well as for increasing physical activity levels in patients with musculoskeletal pain [21].

Therefore, we will investigate the efficacy of a multimodal physical activity intervention consisting of supervised exercises, health coaching and provision of an activity monitor on physical activity levels, pain intensity and disability compared to supervised exercises plus sham coaching and sham activity monitor in patients with chronic, nonspecific LBP. Our primary hypothesis is that the physical activity intervention will increase physical activity levels as well as reduce pain intensity and disability at 3 months post randomisation. The secondary outcomes are physical activity, pain intensity and disability at 6 months and 12 months post randomisation as well as other objective measures of physical activity (i.e. time spent doing light and moderate-vigorous physical activity, number of steps), self-reported physical activity levels, depression, pain self-efficacy, perceived recovery, weight-related outcomes and quality of life measured at 3-, 6- and 12-month follow-ups.

## Methods

### Design

This study will be a parallel randomised controlled trial (RCT) conducted at two outpatient physical therapy clinics in Presidente Prudente, Brazil. This protocol conforms to the Consolidated Standard of Reporting Trials (CONSORT) Statement and is registered at ClinicalTrials.gov (NCT03200509). Figure 1 shows the study design. The Standard Protocol Items: Recommendations for Intervention Trials (SPIRIT) Checklist is provided in Additional file 1 and the SPIRIT Diagram is included in the Fig. 2.

**Fig. 1 Fig1:**
[figure not shown]
Study design

**Fig. 2 Fig2:**
[figure not shown]
Details of the schedule of enrolment, interventions and assessments according to Standard Protocol Items: Recommendations for Intervention Trials (SPIRIT) Diagram

### Sample size

A sample size calculation was performed based on an objective measure of physical activity level, i.e. counts per min, derived from an accelerometer. A total of 160 participants (80 patients per group) will be required to detect a 20% between-group difference in physical activity levels (mean difference between groups of 59.2 counts per min, a standard deviation of 111.6 counts per min) with a power of 0.80, alpha of 0.05 accounting for a 15% loss to follow-up. The counts per min parameters used in the sample size calculation are from a previous study conducted with a similar population [22]. The total of 160 participants is enough to detect a between-group difference of 1 point (standard deviation (SD) = 1.84) in the numerical pain rating scale and of 4 points (SD = 4.9) in the Roland Morris Disability Questionnaire (RMDQ) with a power of 80%, an alpha of 0.05 and 15% dropout as reported in a previous trial with this population [23].

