### Data analysis

Continuous variables will be reported using mean (standard deviation) or median (interquartile range), depending on the data distribution, and dichotomous and categorical variables will be reported using frequencies (proportion). All data will be analysed following intention-to-treat principles. The difference between groups will be analysed with linear mixed models using fixed effects for group, time and group-versus-time interaction and random intercepts for individuals to account for the dependence of repeated measures. Statistical significance will be set at 0.05. We will report the number of participants with missing scores for each outcome. The statistical software SPSS V.20.0 (IBM corporation, Somers, NY, USA) will be used for data analysis. Planned subgroup analyses will investigate differences in effects of the intervention by physical activity levels at baseline assessment and pain self-efficacy. In addition, we will also conduct secondary analyses to investigate the treatment effects considering the adherence to treatment using a complier average causal effect (CACE) approach.

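### The accelerometer inputs call for about 132–136 participants, not the 160 given as required; 160 gives about 87% power for counts per minute, not 80%

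*Protocol article*

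**What the plan says.** The Sample size section bases the calculation on accelerometer counts per minute. It gives all the inputs in one sentence: a "mean difference between groups of 59.2 counts per min", "a standard deviation of 111.6 counts per min", and then "with a power of 0.80, alpha of 0.05 accounting for a 15% loss to follow-up". The result is presented as a requirement: "A total of 160 participants (80 patients per group) will be required to detect a 20% between-group difference in physical activity levels".

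A second sentence takes the total of 160 as given. It says this is sufficient for a 1-point difference in pain (SD 1.84) and a 4-point difference on the Roland Morris Disability Questionnaire (SD 4.9), at the same power, alpha and dropout.

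The section does not state whether alpha is one- or two-sided. It mentions no design effect, multiplicity allowance, rounding margin or other addition. The Data analysis section repeats the same level: "Statistical significance will be set at 0.05".

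**The concern.** The inputs and the result stand in the same sentence, so a reader can check one against the other, and they do not agree. The standardised difference is a little over 0.5, which at 80% power and two-sided 0.05 needs fewer than 60 completers per group. A 15% allowance does not lift that to 80.

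What is at stake is the reproducibility of the main sample-size calculation and the power quoted from it. As written, 80% power is attached to a difference of 59.2 counts per minute. On the protocol's own assumptions the trial has more power than that, and could detect a somewhat smaller difference at 80%. Someone citing the design later would quote the wrong pairing of size, difference and power. No participant or analysis is put at risk.

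**Working it through.** **Inputs** (Protocol article, Sample size): difference 59.2; SD 111.6; power 0.80; alpha 0.05; loss 15%; equal groups. Sidedness is not stated, so two-sided is assumed and one-sided is shown as a variant.

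**Attempt to reproduce 160**

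1. Standardised difference: d = 59.2 / 111.6 = 0.5305.
2. Normal approximation: n per group = 2 × (1.960 + 0.842)² / d² = 2 × 7.849 / 0.2814 = 55.8, so 56.
3. t-test (smallest n for which the noncentral t with 2n − 2 degrees of freedom and noncentrality d√(n/2) gives power of at least 0.80): 56.8, so 57.
4. Allowance for 15% loss: 56 / 0.85 = 65.9, so 66 per group and 132 in total; 57 / 0.85 = 67.1, so 68 per group and 136 in total. Without rounding before inflation, the t-test gives 56.8 / 0.85 = 66.8, so 67 per group and 134 in total.
5. Against the stated 160: 160 − 136 = 24 and 160 − 132 = 28 participants, or 15% to 17.5% of 160.

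**Other conventions**

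| Variant | Total after 15% allowance |
|---|---|
| Two-sided 0.05, power 0.80, divide by 0.85 | 132 (z), 136 (t) |
| Same, multiply by 1.15 instead | 130 (z), 132 (t) |
| One-sided 0.05, power 0.80 | 104 (z), 106 (t) |
| Two-sided 0.05, power 0.85 | 152 (z), 154 (t) |
| Two-sided 0.05, power 0.90 | 178 (z), 180 (t) |

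None of the variants that use alpha 0.05 and power 0.80 gives 160.

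**What 160 delivers for counts per minute**

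- Completers: 80 × 0.85 = 68 per group.
- Power: d√(68/2) = 0.5305 × 5.831 = 3.093; Φ(3.093 − 1.960) = Φ(1.133) = 0.871. The t-test gives 0.867.
- Difference detectable with 80% power: 2.802 × 111.6 × √(2/68) = 53.6 by the normal approximation, and 54.0 by the t-test.
- Loss that still leaves 80% power: 1 − 57/80 = 28.75%.

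**Pain and disability at 68 completers per group**

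- Pain: d = 1 / 1.84 = 0.543. Needs 54 (z) or 55 (t) per group, which is 128 or 130 in total after loss. Power is 88.7% (z) or 88.2% (t).
- Disability: d = 4 / 4.9 = 0.816. Needs 24 (z) or 25 (t) per group, which is 58 or 60 in total after loss. Power is 99.7%.

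For both outcomes 160 exceeds the need, so the second sentence of the section is right.

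**The case against.** The strongest reply is that the discrepancy is harmless. The trial is larger than its inputs need, the claim in the Discussion that it is sufficiently powered for its primary outcomes holds on those inputs, and a null result will be judged from its confidence interval rather than from planned power. The article is also condensed, so a full protocol might record a margin. All of this bears on importance, and it stands: this is a reporting error in the cautious direction. It does not rescue the sentence, which gives 160 as the number required from the inputs printed beside it.

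Two stronger readings are tempting.

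- **That the origin of 160 can be identified.** A reader might notice that applying the 15% twice leads to 80 per group (57 to 68, then 68 / 0.85 = 80). So does two-sided alpha 0.025 by the normal approximation (68 / 0.85 = 80), which might suggest an undeclared multiplicity allowance. The document supports neither. At alpha 0.025 the t-test needs 69 completers, and 69 / 0.85 = 81.2, so 82 per group. With three primary outcomes an equal split would be 0.05/3, not 0.025, and both sections print 0.05. Power of about 0.87 with 15% loss, 80% power with about 29% loss, or plain rounding up would lead to 80 equally well.
- **That the surplus quietly pays for three primary outcomes.** It does not: with 68 per group, power for counts per minute at alpha 0.05/3 is about 75%.

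**Conclusion.** The point holds for the counts-per-minute sentence only. Its inputs require about 132–136 participants, and 160 is 24 to 28 more. At 160 with 15% lost, power is about 87% rather than 80%, and the difference detectable at 80% power is about 54 rather than 59.2 counts per minute.

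This rests on a two-sided test at 0.05 and a plain comparison of two means; the section gives no within-person correlation that would tie the number to the planned mixed model. A one-sided test would widen the gap. The 87% further assumes that loss is exactly 15% and that every completer supplies a valid accelerometer record; it would be lower if some wear weeks fail the validity rule.

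The error is conservative and gives no reason to change enrolment or analysis.

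**What to change.** Keep 160 and correct the sentence in one of two ways.

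- Restate it, for example: *About 132–136 participants give 80% power for counts per minute after 15% loss at two-sided 0.05; 160 give about 87%.*
- Or, if other inputs or a deliberate margin produced 160, print them.

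In either case, say that alpha is two-sided if that is what was used. The pain and disability sentence can stay as it is. The cost is a text edit, with no change to recruitment, follow-up or analysis.

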### Participants

Participants with nonspecific LBP seeking care at two outpatient physiotherapy clinics will be invited to participate in this trial. The recruitment will start in August 2017 and is expected to finish in December 2018 with final data collection (12-month follow-up) in December 2019. Patients with chronic, nonspecific LBP, defined as pain and discomfort localised below the costal margin and above the inferior gluteal folds, with or without leg pain and of at least 3 months’ duration, will be included if they are aged between 18 and 60 years. Participants who have serious spinal pathology (e.g. tumours, fractures and inflammatory diseases), nerve root compromise (i.e. at least two of the following signs: weakness, reflex change, or sensory loss associated with the same spinal nerve), spinal surgery, pregnancy, illiteracy, insufficient understanding of the Portuguese language, cardiorespiratory diseases, fibromyalgia or any other musculoskeletal condition that may affect activity and movement will be excluded.

A screening assessment to check the eligibility criteria will be undertaken by a trained physiotherapist. Then, participants who meet the eligibility criteria will be provided with verbal and written information about the purpose of the study. Participants who agree to participate in the study will be asked to give written informed consent before the baseline assessments.

### Procedures

After baseline assessment, the participants will be randomised to the intervention or the control group. Randomisation will be undertaken using a random sequence of numbers generated by computer software (Microsoft Excel). This sequence will be generated and inserted in opaque and sealed envelopes by a research assistant. After baseline assessment, the treating physiotherapist will open the envelope, reveal the treatment allocation and deliver the interventions. The treating physiotherapist will not be blinded to group allocation due to the nature of the intervention. Trained assessors blinded to group allocation will be responsible for outcome measurement.

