### Outcomes

The measures will be collected using REDCap (Research Electronic Data Capture) [31] hosted at Sao Paulo State University. Data will be collected and stored in spreadsheets by assessors blinded to group allocation. At baseline assessment, the physiotherapist assessors will collect data on participant characteristics (i.e. age, gender, educational level, presence of comorbidities, medication use and employment status). To characterise the study participants, information on fear of movement measured with the Tampa Scale for Kinesiophobia (TSK) [32] and prognosis risk measured with the Örebro Musculoskeletal Pain Screening Questionnaire (ÖMPSQ) [33] will be collected at baseline. Outcome measures will be assessed at baseline, post intervention (i.e. 3 months after randomisation) and at 6 and 12-month follow-ups. Details on the primary and secondary outcomes are reported below:

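### The unblinded treating physiotherapist opens the allocation envelopes, an avoidable risk of selection bias; someone who neither treats nor assesses should release the allocation

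*Protocol article*

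**What the plan says.** All references are to the protocol article.

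- **Preparation (Procedures).** The sequence is a set of random numbers from Microsoft Excel. "This sequence will be generated and inserted in opaque and sealed envelopes by a research assistant".
- **Opening (Procedures).** "After baseline assessment, the treating physiotherapist will open the envelope, reveal the treatment allocation and deliver the interventions". Of the same person it says: "The treating physiotherapist will not be blinded to group allocation due to the nature of the intervention". Outcome assessors are blinded.
- **Order of events (Participants).** "Participants who agree to participate in the study will be asked to give written informed consent before the baseline assessments", so consent precedes the envelope. On screening: "A screening assessment to check the eligibility criteria will be undertaken by a trained physiotherapist". Whether this physiotherapist also treats is not stated.
- **Sites (Design).** The trial is "conducted at two outpatient physical therapy clinics in Presidente Prudente, Brazil". How patients divide between the clinics is not given.
- **Analysis (Data analysis).** The fixed effects are group, time and their interaction, with a random intercept per person. Clinic is not listed.
- **Data system (Outcomes).** "The measures will be collected using REDCap (Research Electronic Data Capture) [31] hosted at Sao Paulo State University". No randomisation function is mentioned.

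**The concern.** Concealment should keep each assignment out of the hands of anyone with a stake in it until it is irrevocable. Here the article itself fixes that the therapist opens the envelope, so this is a stated choice and not a detail lost in condensing the protocol.

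The opener may have views on who would profit from coaching. Table 1 (item 5) describes one kind of provider, trained in both health coaching and active listening. The same therapist may therefore serve both arms and know past allocations. A patient would be unlikely to notice an exchange, because the sham is designed to be credible (Control group).

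If patients with a better outlook were moved towards coaching, the arms would differ in prognosis for reasons other than chance. Analysis by intention to treat would then preserve the recorded assignment, including a steered one. Motivation, an obvious ground for steering, is not among the baseline measures listed under Outcomes.

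**Working it through.** No figure in the plan underlies this point. The check sets each safeguard against each threat, and then gives illustrations under labelled assumptions.

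**1. What each safeguard covers**

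- Opaque, sealed envelopes prepared by someone else hide the assignment until opening. They do not control what the opener does next.
- Consent and baseline before opening limit selective enrolment. They do not stop an envelope being held back or exchanged between two enrolled patients.
- Blinded assessors protect measurement, not allocation.
- The article describes no link between an envelope and a participant before opening. The full protocol may contain one.

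**2. Illustration of size**

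Inputs from Sample size: 80 per arm; SD 111.6 counts per min, 1.84 pain points and 4.9 RMDQ points; target difference 59.2 counts per min. Assumed: k exchanged pairs, the two patients in a pair differing by d SD in expected outcome. Each exchange raises one arm's mean by d/80 and lowers the other's by d/80, so the shift is 2kd/80.

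| k | d (SD) | Shift (SD) | Counts per min | Share of 59.2 |
|---|---|---|---|---|
| 1 | 0.5 | 0.0125 | 1.4 | 2% |
| 1 | 1 | 0.025 | 2.8 | 5% |
| 4 | 0.5 | 0.05 | 5.6 | 9% |
| 4 | 1 | 0.10 | 11.2 | 19% |

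In the last row the shift is also 0.10 × 1.84 = 0.18 pain points and 0.10 × 4.9 = 0.49 RMDQ points. Neither k nor d has a source in the documents.

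**3. Clinic (secondary)**

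Assume 80 patients per clinic and no stratification. The chance of a 48:32 or worse split in a given clinic is then 9.3% under simple randomisation (binomial) and 1.7% with one fixed list of 80 and 80 (hypergeometric). In an assumed clinic of 40, a split of 24:16 or worse has a chance of 27% or 20% respectively.

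Suppose the clinics split 48:32 and 32:48 and their mean outcomes differ by an assumed 0.25 to 0.5 SD. The realised shift is then 0.25 × 111.6 × (48/80 − 32/80) = 5.6 to 0.5 × 111.6 × (48/80 − 32/80) = 11.2 counts per min. Over repeated randomisations it averages zero.

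Unequal arm sizes cost little. With 160 × 0.85 = 136 evaluable, power is Φ(59.2 / (111.6 × √(1/n₁ + 1/n₂)) − 1.96). This gives 87% at 68:68 and 86% at 82:54.

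**The case against.** The strongest reply is that the article already has most of what good concealment needs. A research assistant generates the sequence and prepares opaque, sealed envelopes, and allocation follows consent and baseline. Nothing says that the treating physiotherapist screens or enrols. What is left is deliberate tampering, and a seal exists to show it. Being unblinded after opening is not a failure of concealment, and the article discloses the lack of therapist blinding. All of this stands, and it limits the point to a residual risk. It does not answer why the interested person should perform the last step.

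A reader might also infer several stronger claims that the documents do not support:

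- **One list that ignores the clinics.** Procedures speaks only of a random sequence. It does not say whether there is one list or two, or whether it is blocked, and an article may leave this to the full protocol. The most that can be said is that stratification is not described.
- **Clinics with their own physiotherapists and classes.** No section says so, and an argument from differences between operators has no basis here.
- **Clinic imbalance as bias.** It is chance imbalance, does not bias the comparison on average and costs almost no power. Missing an exact 80:80 split is no defect.
- **A shift that no analysis could remove.** This is too strong. Outcomes are measured at baseline. If baseline is a level of time in the model, a stable difference in the outcome itself separates from the change. Unmeasured prognosis would escape.

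**Conclusion.** The point holds as a risk built into a stated procedure: the unblinded person who delivers the intervention also opens the envelope. The documents show no steering and no broken concealment, and the size of any bias cannot be derived from them. The figure of 0.10 SD, about 11 counts per min or 19% of the target, rests wholly on the assumption of 4 exchanged pairs differing by 1 SD. Smaller assumptions give 1.4 to 5.6 counts per min. Such a shift would be systematic, unlike chance imbalance, which is why the step is worth changing although the risk may be small.

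The clinic point is minor. It concerns precision and protection against an unlucky split, and its figures depend on assumed clinic sizes and differences.

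**What to change.** For participants still to be randomised (Trial status expects recruitment to run to December 2018), use one of two routes:

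- A person who neither treats nor assesses, for example the research assistant, holds sequentially numbered envelopes, writes the participant's ID on the next one, and only then opens it. Anyone who knows the sequence should also take no part in screening.
- The electronic data system releases the allocation, if the installation in use offers a randomisation function. The article does not say whether it does.

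Under either route, release follows completed consent and baseline, and the treating physiotherapist is told the result. Participants already randomised keep their allocation.

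Add clinic as a fixed effect in the mixed model, and state whether the list is stratified by clinic.

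The cost is a short amendment and one model term, and the sample size does not change. The downside is practical: the independent person, or online access, must be available whenever a participant is allocated.
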